### Data collection and management

Personnel involved in data recording and evaluation will undergo comprehensive training in clinical research methodology and data management to ensure data quality, including accuracy, integrity, consistency, and timeliness throughout the collection process. The standardized process will be followed to collect data, check the input data, and ensure the quality of the data. If problems in data verification are identified, they will communicate with the researchers in time and record the question and answer process. These evaluation criteria and processes will provide reliable research support.

### Statistical analysis

First, ANOVA analysis assumes that all continuous variables satisfy the normality and homogeneity of variance. If the test finds a violation of the assumption, a non-parametric alternative method will be used. For repeated measurement data (such as fMRI), the spherical hypothesis is satisfied by default. And if the hypothesis is found to be violated, the Greenhouse–Geisser will be used to correct the degrees of freedom. All analyses follow the intention-to-treat (ITT) principle, and the missing data are carried out by the last observation carried forward (LOCF).

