##### The CRS-R score

Patients’ recovery of consciousness is rated on six dimensions, namely, auditory, visual, motor, speech, communication, and arousal, with scores ranging from 0 to 23. The higher the score of CRS-R, the better the patient’s state of consciousness. According to research, the design of the CRS-R is especially suitable for identifying patients with vegetative states and a minimal state of consciousness (27–29). It includes evaluation indicators that the GCS does not have, such as visual tracking and visual positioning. The CRS-R scale can further divide the state of consciousness into MCS -, MCS+, and eMCS. MCS− includes object localization, visual pursuit or fixation, automatic motor behaviors, object manipulation, and localizing noxious stimuli. MCS+ includes the ability to follow commands, object recognition, comprehensible verbal expression and meaningful communication (30). eMCS includes the functional use of two different objects and functional interactive communication (31). Regarding outcome indicator, data collection should include not only longitudinal changes in the CRS-R score but also the specific temporal dynamics of clinically significant consciousness improvement. This is defined as the time for patients with MCS− to eventually improve to MCS+ or eMCS/patients with MCS+ to eventually improve to eMCS after treatment.

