##### Functional magnetic resonance imaging

Functional magnetic resonance imaging (fMRI) can reflect the changes in blood oxygenation (BOLD), blood flow changes, and other conditions in the functional areas of the brain and then evaluate brain function stereoscopically and intuitively. BOLD-fMRI imaging can reflect dynamic changes in the functional activity of the cerebral cortex through hemodynamic changes following neuronal activity. A 3.0 T superconducting magnetic resonance imaging system (Siemens) will be used to collect imaging data. The gradient echo plane imaging sequence will be used to collect BOLD-fMRI data. Resting-state functional MRI is acquired at the beginning of the scan, and the parameters are as follows: TR = 2,000 ms, TE = 30 ms, flip angle = 90°, FOV = 224 × 224 mm, matrix size = 64 × 64 mm, slice thickness = 3.5 mm, and slice number = 33 slices. BOLD-fMRI will be performed 30 min before the intervention (baseline period) and 30 min after the end of the 4-week intervention (end period).

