### Sample size calculation

The GCS score was used as the primary outcome measure for the sample size calculation, following the method outlined by Lai Shilong in the Methodology of Clinical Research of Integrated Chinese and Western Medicine. Based on a study by Li Yuyuan et al. (25), the GCS score for the acupuncture combined with rTMS group was 10.30 ± 3.47 after 4 weeks of treatment. The GCS score for the acupuncture-only group was 8.33 ± 2.97, whereas that for the rTMS group was 8.16 ± 2.98. Taking *α* = 0.05, two-sided test, and *β* = 0.2, the ratio of the three groups of sample sizes was 1:1:1. After the above values are substituted with PASS 15 software, the sample size required for each group is calculated to be 32 cases. Considering a shedding rate of 20%, 39 patients are included in each group, and 117 patients are ultimately included in this study.

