#### Clinical data analysis

SPSS 25.0 software will be used for data analysis. The measurement data will be normally distributed and expressed as mean ± standard deviation (
$\bar{x}$
 ± *s*). Paired *t*-test will be used for comparisons between groups before and after treatment. One-way analysis of variance will be used for the comparison of differences between the three groups, and the *q*-test will be used for comparisons between groups. The *χ*^2^-test will be used for pairwise comparisons of enumeration data, and the Mann–Whitney test and Wallis rank sum test will be used for comparisons among the three groups. *p* < 0.05 will be considered statistically significant.

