Acupuncture is still based on a summary of clinical experience, and there are various problems in research design. Because coma patients cannot sit autonomously, traditional acupuncture treatment generally involves patients in the supine position. Owing to their position, fewer neck acupoints are selected. This study selects head and neck acupoints and innovatively selects the acupuncture position in which the head of the patient is fixed by a nursing worker or family member to maintain the sitting position. In the previous clinical trial, this study found that acupuncture at neck acupoints can improve the blood supply of the vertebral artery and carotid artery, and the neck acupoints selected by this acupuncture method are close to the medulla oblongata and brainstem reticular structure. Acupuncture may improve the signal of the brainstem reticular ascending activation system, improve the blood supply of the brain, and enhance the compensatory mechanism of the brain. In addition, a sitting position can induce the emergence of proprioception in patients, which can achieve a better curative effect. In addition to the use of the most common behavioral assessment scale, such as the GCS, this study also adds the CRS-R score to accurately determine the level of minimum consciousness and combines objective-specific neurological function laboratory indicators to improve the objectivity and accuracy of the assessment. A follow-up at 4 weeks after the end of treatment will be added to verify that the study had long-term efficacy. NSE and S-100B are specific markers of the central nervous system. Clinical studies have demonstrated elevated NSE levels in both cerebrospinal fluid and peripheral blood shortly after stroke onset (45, 46),while increased S-100B protein concentrations have been consistently observed in cerebrospinal fluid of stroke patients (47, 48). And the degree of cognitive dysfunction in stroke patients is positively correlated with the expression of NSE and S-100B (49). Xu et al. (50) have also confirmed that the expression of NSE and S-100B in the serum of stroke patients is up-regulated after stroke, and the expression is down-regulated after treatment, reflecting that NSE and S-100B can help determine the prognosis of stroke. Therefore, NSE and S-100B will be used as one of the outcome indicators to help verify whether this study has therapeutic significance through the values changes before and after treatment. A reduction in post-treatment NSE and S-100B levels compared to baseline values will indicate therapeutic significance. Brain functional magnetic resonance imaging is an advanced brain function examination tool that can be accurately positioned clinically. BOLD-fMRI reflects neural activity by detecting changes in blood oxygen in the brain, and provides a visual research method for studying changes in brain function (51). However, in the current research on the brain effect of acupuncture based on BOLD-fMRI, Taixi (KI3), Hegu (LI4) and other limb acupoints are the most studied acupoints (52, 53). This study will select head and neck acupoints and use BOLD-fMRI to observe the brain effects during acupuncture objectively and stereoscopically, so as to improve the evaluation of the efficacy of patients with MCS, and further explore the mechanism of functional reorganization of brain regions in MCS patients.

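### The repeated-measures rule is illustrated only by two-scan fMRI, where it cannot act, while GCS and CRS-R have no baseline-adjusted longitudinal analysis and no deciding visit despite a planned follow-up

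*Protocol article*

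**What the plan says.** All references are to the protocol article.

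- **Statistical analysis, opening paragraph.** The repeated-measures provision reads: "For repeated measurement data (such as fMRI), the spherical hypothesis is satisfied by default". Greenhouse–Geisser is used if sphericity is found to be violated. Missing values are filled by last observation carried forward (LOCF).
- **Functional magnetic resonance imaging.** Two scans are scheduled: "30 min before the intervention (baseline period) and 30 min after the end of the 4-week intervention (end period". The MRI data analysis section then uses paired t-tests for change within each group.
- **Clinical data analysis.** Paired t-tests compare before with after treatment. Between arms: "One-way analysis of variance will be used for the comparison of differences between the three groups". A q-test follows for pairs of arms, and p < 0.05 applies throughout. No visit, baseline covariate or repeated-measures model is named.
- **Discussion.** "A follow-up at 4 weeks after the end of treatment will be added to verify that the study had long-term efficacy". This comes directly after a sentence on GCS, CRS-R and the laboratory markers, but it does not say which outcomes are measured at that time.
- **The CRS-R score.** "data collection should include not only longitudinal changes in the CRS-R score"; time to improvement in consciousness category is to be collected as well.
- **Sample size calculation.** "The GCS score was used as the primary outcome measure for the sample size calculation", with values taken at week 4: "the GCS score for the acupuncture combined with rTMS group was 10.30 ± 3.47 after 4 weeks of treatment".

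The assessment schedule is in Figure 2, which is not reproduced in the text available.

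**The concern.** A sphericity rule matters only for an outcome with three or more occasions. The one example given has two. The outcomes that plausibly have three (before treatment, end of treatment, follow-up) are the consciousness scales, and the section on clinical data gives them no method that handles more than one post-treatment value per patient.

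Two things are at stake. First, a one-way ANOVA uses one value per patient. If both post-treatment values are to be compared between arms with the methods listed, the direct route is one ANOVA per visit. With no visit named as deciding and no adjustment across visits, each scale could then give two chances of a significant result. Second, the listed between-arm test ignores the baseline score, although GCS and CRS-R are both recorded before treatment. Precision is lost that would cost no extra data.

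**Working it through.** **1. The plan's own figure.** The article gives no error rate across visits. The nearest figure is the 32 patients per group, which shows the comparison the trial was sized for.

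- Inputs (Sample size calculation): means 10.30, 8.33 and 8.16; SDs 3.47, 2.97 and 2.98; "Taking *α* = 0.05, two-sided test, and *β* = 0.2, the ratio of the three groups of sample sizes was 1:1:1".
- Grand mean = (10.30 + 8.33 + 8.16)/3 = 8.93. Sum of squared deviations = 1.37² + 0.60² + 0.77² = 2.83.
- Noncentrality λ = n × 2.83 / SD². With n = 32 and SD = 2.97, λ = 32 × 2.83 / 8.82 ≈ 10.3. The noncentral F distribution with 2 and 93 degrees of freedom gives 81% power, and n = 32 is the smallest number reaching 80%.
- SD 2.98 also gives 32; the pooled SD of 3.15 gives 35. The article does not say which SD was entered. That is a separate matter.

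So 32 is consistent with a single three-group ANOVA on week-4 GCS, without a baseline covariate or a second visit.

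**2. Can the correction act on fMRI?** For k occasions, ε = tr(M)² / [(k − 1) · tr(M²)], where M is the (k − 1) × (k − 1) covariance matrix of orthonormal contrasts. With k = 2, M is a single number m, so ε = m² / (1 × m²) = 1 for every covariance matrix. A numerical check on three random matrices returned 1.0 each time. The degrees of freedom can never be changed.

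**3. What two ANOVAs on one scale would do.** This step is conditional on two premises that the article does not state: the scale is measured at follow-up, and the ANOVA is run at week 4 and at follow-up with equal standing.

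- Independent tests: 1 − 0.95² = 9.75%.
- Correlated tests, by simulation with no treatment difference, normal data, 39 per arm and 100,000 replicates:

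| Assumed between-visit correlation | P(at least one F-test p < 0.05) |
|---|---|
| 0.5 | 9.1% |
| 0.7 | 8.5% |
| 0.8 | 7.9% |
| 0.9 | 7.0% |

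Simulation error is about 0.1 percentage point (√(0.09 × 0.91 / 100,000) = 0.0009). The article gives no correlation, so every row is an assumption. The excess over 5% is about 2 to 4 points per scale.

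**4. What a longitudinal model adds.** With complete data, a model with unstructured covariance and visit-specific baseline effects gives the same week-4 contrast as an ANCOVA at week 4. The precision gain at week 4 therefore comes from the baseline score: residual variance falls by a factor of about 1 − r², where r is the baseline-to-week-4 correlation (not given). The joint model adds two things: incomplete patients can be used without carried-forward values, and both visits sit in one prespecified analysis.

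**The case against.** Several objections are sound and limit the point.

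- **The rule is not confined to fMRI.** A reader might infer that the provision leaves out the clinical scales. The wording introduces fMRI as an example, in a general paragraph that precedes both the clinical and MRI subsections. If the scales have three occasions, the rule can cover them. The sentence is also literally true for two scans. What stands is that the example is inapt, and that the clinical subsection names no analysis to which the rule would apply.
- **Separate ANOVAs per visit are not stated.** A reader might infer that the plan prescribes them. The clinical subsection does not mention visits at all.
- **Measurement of the scales at follow-up is not stated.** The context makes it likely, but the follow-up sentence lists no outcomes, the schedule figure is not available, and the CRS-R remark on longitudinal change concerns data collection and fixes no third visit.
- **The article leans towards end of treatment.** The sample size uses week-4 values, response is defined by status after treatment, and follow-up has its own purpose. It goes too far to say that efficacy could freely be claimed from the better visit. Still, no sentence says that week 4 decides.
- **LOCF pulls the error figure down.** Carrying week-4 values forward raises the between-visit correlation, towards the 7% end.
- **Model detail often belongs in an analysis plan.** That is fair for covariance structure and similar items. But the article does commit to a particular between-arm test and significance level, and that commitment can be improved.

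**Conclusion.** Two parts follow directly from the text. The Greenhouse–Geisser rule cannot act on its only example. The clinical analysis as written has no baseline adjustment, no longitudinal model and no deciding visit, although a follow-up is planned to support a statement of long-term efficacy.

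The error rate is conditional. If GCS and CRS-R are measured at follow-up, and the listed ANOVA is applied at both visits with equal standing, the chance of at least one false-positive F-test is about 7% to 9% per scale, for assumed correlations of 0.9 to 0.5. It should not be read as the plan's established error rate. It also leaves out multiplicity across the several main outcomes and across pairs of arms, which is a separate issue.

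The point is worth acting on because the remedy is cheap and uses data that the trial collects anyway. The inapt example alone would not justify a change in analysis.

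**What to change.** - **Model.** Analyse GCS and CRS-R each in a mixed model for repeated measures with arm, visit, arm-by-visit, baseline score and baseline-by-visit. Use observed values only. LOCF-filled values would forfeit the model's advantage with missing data, so the LOCF sentence must be amended for these two outcomes.
- **Deciding visit.** State that the week-4 arm contrast decides, which matches the values used for sizing. Test the follow-up contrast only if week 4 is significant, and report it as evidence of durability. A false positive then requires a significant week-4 result first, so the chance across the two visits stays at 5% per scale for the three-arm test.
- **Follow-up outcomes.** State which outcomes are measured 4 weeks after treatment. If the scales are not among them, the model reduces to a week-4 ANCOVA, and the long-term efficacy aim must be reconciled with what is measured.
- **Wording.** Replace fMRI as the repeated-measures example. This changes no result.

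The cost is analysis-plan text, settled before the outcome data are examined. SPSS 25 fits the model, and no further patients or visits are needed. The downside is that follow-up can no longer stand alone as evidence of efficacy.

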### Criteria for termination of the study

The study will be terminated when the following situations occur: poor compliance of patients after enrollment and non-cooperation with experimental research; during the treatment, critically ill patients need to be transferred to other departments or hospitals for treatment; the patient’s immediate family members request to withdraw from the study.

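### LOCF is fixed as the only missing-data method, although one listed exit is tied to outcome, fMRI has only two scans, and outcome collection after exit is left unstated

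*Protocol article*

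**What the plan says.** Under Statistical analysis, the protocol article sets one rule for everything: "All analyses follow the intention-to-treat (ITT) principle, and the missing data are carried out by the last observation carried forward (LOCF"). No other missing-data method and no sensitivity analysis is named.

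The section Criteria for termination of the study lists three reasons, all about individual patients:
- "poor compliance of patients after enrollment and non-cooperation with experimental research";
- "critically ill patients need to be transferred to other departments or hospitals for treatment";
- a patient's "immediate family members request to withdraw from the study".

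It does not say whether GCS, CRS-R, serum markers or fMRI are still obtained after such an exit.

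Three other places matter.
- **fMRI (Outcome measures).** There are two acquisitions only: "BOLD-fMRI will be performed 30 min before the intervention (baseline period) and 30 min after the end of the 4-week intervention (end period"). MRI data analysis then uses paired t-tests within groups and a Pearson correlation between scale improvement and fMRI change.
- **Follow-up (Discussion).** "A follow-up at 4 weeks after the end of treatment will be added to verify that the study had long-term efficacy".
- **Sample size calculation.** It assumes 4-week GCS of 10.30 (SD 3.47), 8.33 (SD 2.97) and 8.16 (SD 2.98), with 32 per group raised to 39 for 20% loss.

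**The concern.** LOCF is neutral only if a patient's state would have stayed where it was last seen. One of the three exits, critical illness needing transfer, contradicts that directly in a trial of consciousness: the carried score comes from before the deterioration.

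The method also works mechanically in two places. With two fMRI scans, a missing end scan can only be replaced by the baseline scan. The change is then exactly zero, and that zero enters the paired tests and the correlation as if measured. For anyone seen at week 4 and lost before the later follow-up, LOCF makes the two values equal, so persistence is assumed for that patient.

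The planned paired t-tests and one-way ANOVA treat imputed values as observed, so the standard errors do not reflect the missing information.

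At stake are the GCS, CRS-R total, NSE, S-100B and fMRI comparisons. The arms differ in burden (seated neck electroacupuncture, rTMS, or both in sequence), so unequal exit is possible, although nothing in the document shows that it will occur.

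**Working it through.** **1. The plan's own sample size.** For a three-group one-way ANOVA at α = 0.05, the grand mean is (10.30 + 8.33 + 8.16)/3 = 8.93, and the sum of squared deviations is 1.37² + 0.60² + 0.77² = 2.83. With SD 2.975 (midway between 2.97 and 2.98) and n = 32, the noncentrality is 32 × 2.83/2.975² = 10.23 and power is 0.81. The stated 32 per group reproduces. With the root-mean-square SD of 3.15, power at 32 is 0.76. The stated 39 is 32 × 1.2 = 38.4 rounded up; 32/(1 − 0.2) gives 40.

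**2. How many values could be carried.** 0.20 × 39 = 7.8 per arm; 0.20 × 117 = 23.4 in total.

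**3. If every dropout carries a common baseline b** (20% loss in each arm, SDs as planned). The difference between the combined and acupuncture arms becomes (0.8 × 10.30 + 0.2b) − (0.8 × 8.33 + 0.2b) = 0.8 × 1.97 = 1.58. Power for a two-sided t-test uses pooled SD √((3.47² + 2.97²)/2) = 3.23 and noncentrality δ/(3.23 × √(2/n)). The overall F test is at SD 2.975.

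| Analysis | n per arm | Difference | Pairwise power | Overall F power |
|---|---|---|---|---|
| No loss | 39 | 1.97 | 0.76 | 0.89 |
| Completers | 31 | 1.97 | 0.66 | 0.80 |
| LOCF, all carry baseline | 39 | 1.58 | 0.57 | 0.70 |

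At SD 3.15 the last two F-test entries are 0.75 and 0.65. The fair comparator for LOCF is the completer row, because losing patients costs power under any method. The part due to LOCF is therefore 0.66 − 0.57 = 0.09 for the pairwise test, out of a total drop of 0.76 − 0.57 = 0.19.

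**4. If lost patients deteriorate after the last score.** The GCS values here are assumptions, not in the document: carried score 7 to 8, true later score 3 to 5, so an error of 2 to 5 points per patient.
- Arm mean, with 20% lost and all of them deteriorated: overstated by 0.20 × 2 = 0.4 to 0.20 × 5 = 1.0 points. This goes straight into the before/after tests.
- Between arms, equal loss and equal deterioration: shift of 0.
- Between arms, 25% against 15%: shift of 0.10 × 2 = 0.2 to 0.10 × 5 = 0.5.
- Between arms, 30% against 10%: shift of 0.20 × 2 = 0.4 to 0.20 × 5 = 1.0.

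The sign depends on which arm loses more. The planned difference is 1.97.

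**5. CRS-R categories.** Under Efficacy evaluation, regression and no change both count as ineffective. A deteriorating patient carried at baseline is therefore classified correctly. Only someone who improved and then worsened before the final assessment would be miscounted.

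**The case against.** The strongest reply is that LOCF is declared in advance, that a statistical analysis plan not shown may add sensitivity analyses, and that the harm is easily overstated. Much of the last part stands. A reader might infer four stronger conclusions that the document does not support.

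- **That patients who do badly are systematically removed.** Only one of the three exits is deterioration. A non-compliant patient, or one withdrawn by the family, may have been improving, and LOCF would then understate the result.
- **That assessment stops at exit, in breach of ITT.** The termination section does not say so, and the analysis section invokes ITT for all analyses. The fair criticism is that collection after exit is unclear.
- **That LOCF alone takes power from 0.76 to 0.57.** About half of that drop is the loss of patients itself. The 0.57 also requires every dropout to carry baseline. The assessment schedule is in a figure that is not shown, so interim scale scores may exist. Nor is the shrinkage to 1.58 always bias: if lost patients truly ended alike in all arms, 1.58 would be the right difference among all randomised.
- **That long-term efficacy is shown by construction.** This applies only to patients lost between week 4 and the follow-up, not to the follow-up comparison as a whole.

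What does not stand is the appeal to an unseen analysis plan. LOCF is fixed in the text as the method for all analyses, so this is a stated choice open to criticism and not a detail left for later. Nor does the reply help with fMRI, where interim scans are not planned and a carried baseline yields a zero change whatever the reason for loss.

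**Conclusion.** The concern holds in limited form, at should-fix level. LOCF is a poor main method here because at least one exit depends on outcome, because a missing end scan becomes an fMRI change of zero, and because it assumes persistence for patients lost after week 4. Up to about 23 of 117 outcomes could be imputed.

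The size depends on assumptions. If every dropout carries a common baseline, 20% are lost per arm and the SDs stay as planned, LOCF gives pairwise power of 0.57 against 0.66 for completers, and overall F-test power of 0.70 against 0.80. With unequal removal of deteriorating patients, and the assumed GCS values, the difference between arms shifts by 0.2 to 1.0 points in an unknown direction. With equal removal and deterioration the shift is zero, though within-arm changes stay distorted. The CRS-R effective/ineffective classification is little affected.

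**What to change.** - **Main method.** Replace LOCF with a likelihood-based repeated-measures model, or multiple imputation, under missing at random, using baseline and any interim scores.
- **fMRI.** Analyse observed pairs of scans, or use the same kind of model. Do not carry the baseline scan forward.
- **Sensitivity analyses.** Keep LOCF as one. Add one that allows worse outcomes after transfer for deterioration, because missing at random may not hold for those patients. Assigning them a fixed worst rank is not recommended as the default: it would override any scores collected after transfer, and it is a debatable choice of estimand.
- **Termination section.** State that leaving treatment does not by itself end outcome collection, where collection remains feasible and consent to it stands.

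The cost is protocol wording, some extra analysis work, and some effort to obtain scores for transferred patients. That last item is not free, since the protocol requires trained, certified evaluators who do not know the allocation. It should be settled early, because outcomes not collected cannot be recovered later.
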